### **3.5.3 Secondary outcomes: definition and measurement**

#### **a) Immunogenicity:**

A sub-sample of girls will be assigned to the part of the study measuring the immunogenicity and comparing seropositivity and antibody geometric mean titers (for HPV types 6, 11, 16, 18) in the two study groups.

The first 500 participants recruited will participate to the immunogenicity section of the study (250 per group). A blood sample will be collected at month 60, 90 and 120 following the beginning of vaccination in these participants. Five milliliters of blood will be collected in an 8.5 ml marbled-tube. Only 350 participants will have a blood sample at month 90.

A non-competitive serologic Luminex platform developed by the Quebec public health laboratory (Laboratoire de santé publique du Québec, LSPQ) will be used to detect and quantify HPV types' specific antibodies. This test is sensitive, replicable and quite simple to use(76,77). Depending of

the availability of the LSPQ Luminex platform, laboratory assays could be performed at the Centers for Disease Control and Prevention (CDC, Atlanta, USA) using multiplex direct IgG ELISA to HPV L1+L2 virus-like particles (VLPs) on Meso Scale Discovery platform as previously described with minor modification(78).

Clinical samples from the Vaccine Research Team CHU de Québec-Université Laval biobank (Nagano project #B12-06-986) will be used by the Frederick National Laboratory for Cancer Research (NIH/CDC) for the "9v HPV seronegatives to harmonize threshold" project to develop and validate HPV serological tests.

b) Primary outcome up to 13 years

HPV-16 and HPV-18 infections that persist at least 6 months will be measured, and this, up to **13 years** following the first injection as defined in 3.5.2.

c) Immunogenicity for 5 other types:

A sub-sample of girls will be assigned to the part of the study measuring the immunogenicity and comparing seropositivity and antibody geometric mean titers (for HPV types 6, 11, 16, 18 **and 31, 33, 45, 52, 58**) in the two study groups.

d) Condylomas:

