### 3.8.2 Sample size for the immunogenicity section

Various options for the calculation of the sample size needed for the immunogenicity section were analyzed. Various laboratory tests (cLia, total IgG, neutralizing antibodies, etc.) were performed during previous studies on the topic, resulting in an important heterogeneity in seropositivity levels and antibody titers reported after 2 or 3 doses of Gardasil®(32,34,35).

Taking into consideration that there is no « gold standard » for the laboratory tests measuring antibodies against HPV and that the sensitivity of the tests currently used varies significantly from one test to another, it was decided not to base the sample size calculation on seropositivity. We have assumed appropriate to base our sample size calculation on the ratio of geometric mean titers (GMT) expected in the 2 study groups (GMT2/GMT3).

The lower limit of the GMT ratio's confidence interval was set at 0.5, given that it is generally the case in this type of study(85,86). Because of potential clinical impacts, and future public health decisions, we want to have enough statistical power to detect a ratio  $\geq 0.65$  between the groups. To demonstrate a ratio of 0.65 between GMT2/GMT3 with a lower limit higher than 0.5, a statistical power of 90% and a significance level of 5%; the sample size needed is a total of 138 participants assessed per group at the end of the study (Table 2).

Taking into consideration a full respect of the study protocol (per-protocol) of 80 to 90% and a loss to follow up of about 5% per year, the enrolment of 500 participants (250 per group) was deemed necessary to be able to establish non-inferiority between the two study groups with a statistical power  $\geq 90\%$  ( $\alpha = 5\%$ ). The enrolment of 500 participants at the beginning of the study (month 60 post primary immunization) will enable us to have at least 138 participants assessed at the end of the study.

Table 2. GMT2/GMT3 ratio: non-inferiority test with a lower limit set at 0.5

| Lower limit | Ratio | N per group |
|-------------|-------|-------------|
| 0.5         | 0.55  | 1034        |
| 0.5         | 0.6   | 284         |
| 0.5         | 0.65  | 138         |
| 0.5         | 0.7   | 84          |

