### 3.9 Analysis

Descriptive analyses will be used to describe the participants and compare the two study groups. Specifically, the following analyses will be performed for each of the objectives mentioned in section 2.

For the primary objective:

A survival analysis (time to event analysis) will be performed in order to answer the main study questions. This approach will take into consideration the different duration of follow-up resulting from the fact that the date of entry in the cohort will vary between participants. Time 0 will be defined as the date of randomization. The time of event will be defined as the first occurrence of a persistent infection. Participants with no persistent infection will be censored (right-censored) at: (a) loss to follow-up, (b) death or (c) end of the study whichever comes first. The preliminary analyses will include the comparison of the Kaplan-Meier curves using a non-parametric test (*log-rank test*, *Wilcoxon*) describing how the proportion of participants developing a persistent infection varies over time in each group. The main non-inferiority analysis will rely on the Hazard ratio's (HR) 95% confidence interval. Adjusted analyses will take into consideration the potential confounding factors collected with the annual questionnaire. If the HR's upper limit is not higher than 1.05 (representing a 5% difference of efficacy between the two schedules), we will conclude to a non-inferiority of the 2-dose calendar.

This analysis will then be repeated with the « intention-to-treat » method to evaluate the differences generated by a change in the exposure's definition. Sensitivity analyses will also be performed to evaluate the impact of modifying the outcome's definition. Indeed, it is likely that some girls will not exactly respect the vaginal self-samplings' schedule. We will vary the primary outcome's definition (e.g. consider as persistent infection only if the sample were consecutive and 6 months apart, or

consider as persistent infection a situation where the same type of virus was identified in two consecutive samples regardless of the number of months between the samples).

For the secondary objectives on immunogenicity (objectives 2.2.a and c), two analyses will be performed to measure non-inferiority at month 120:

1) An intention-to-treat analysis (*ITT analysis*) in which all the serologic results available will be included.

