2) A per protocol (*according to the protocol, ATP analysis*) which will only include the participants who respected all the procedures planned in the protocol related to the immunogenicity analysis.

All the statistical tests will be performed with a type I error set at 5%. Percentages of seropositivity will be compared with a Chi square or Fisher test. GMTs will be compared with a *t*-test.

Among seropositive samples, GMTs will be calculated for each of the 3 time points planned in the protocol. GMTs obtained in the two groups at different study points will be compared using an analysis of variance (ANOVA) and a Duncan's multiple range test performed with SAS version 9.1.

For the other secondary objective on condylomas (2.2.d), we will mainly perform descriptive analyses as described at the beginning of this section.

An exact poisson regression is planned at the end of the study to compare the persistent infections observed among the vaccinated girls of the two study groups to that of an historical cohort of unvaccinated girls. Therefore, we will be able to calculate the number of persistent infections prevented by vaccination i.e. the difference between the expected and observed number of persistent infections (2.2.e).

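### Section 3.9 announces a month-120 immunogenicity non-inferiority analysis but names only difference tests, does not carry over the 0.5 limit on GMT2/GMT3, and leaves seropositivity without a margin

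*Protocol*

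**What the plan says.** Section 3.9 of the protocol introduces the immunogenicity objectives 2.2.a and 2.2.c by stating that "two analyses will be performed to measure non-inferiority at month 120", one by intention to treat and one per protocol.

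Section 3.8.2 supplies a criterion: "The lower limit of the GMT ratio's confidence interval was set at 0.5". It sizes the subset on that criterion: "To demonstrate a ratio of 0.65 between GMT2/GMT3 with a lower limit higher than 0.5, a statistical power of 90" per cent, which leads to 138 girls assessed per group at the end of the study.

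The methods in section 3.9 follow, under a general 5% type I error:

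- For titres: "GMTs will be compared with a *t*-test".
- For seropositivity: "Percentages of seropositivity will be compared with a Chi square or Fisher test".
- Over time: "GMTs obtained in the two groups at different study points will be compared using an analysis of variance (ANOVA") together with Duncan's multiple range test.

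Section 3.9 gives no margin, ratio, interval or decision rule for immunogenicity. No seropositivity margin appears anywhere in the protocol. In the same section the primary objective does receive a rule, based on the upper confidence limit of the hazard ratio.

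On sampling, section 3.5.3 a) states: "A blood sample will be collected at month 60, 90 and 120 following the beginning of vaccination in these participants" (month 90 in only 350 of them).

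**The concern.** A test of equality asks whether the GMT ratio differs from 1. The subset was sized to ask whether the ratio lies above 0.5. These are different hypotheses, and the protocol plans for a true ratio of 0.65, well below 1. At that value the named t-test is almost certain to report a difference, even in the trials that meet the 0.5 criterion. An analyst who follows 3.9 literally could therefore report that the two-dose schedule fails on titres when the criterion behind the sample size has been met.

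For seropositivity the problem runs the other way. With no margin, a non-significant chi-square or Fisher result could be taken as support for non-inferiority, although it shows only that no difference was detected.

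This goes beyond detail that a protocol may leave to a statistical analysis plan. The protocol fixes specific procedures, and as fixed they do not serve the purpose it states for them.

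**Working it through.** **Inputs.** From 3.8.2: lower limit 0.5, planning ratio 0.65, power 90%, significance level 5% (sidedness not stated), 138 per group, 250 per group enrolled, 80 to 90% per-protocol, about 5% loss per year. The SD of log titre is not given and has to be back-solved.

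**Reproducing the plan's figure.** On the natural-log scale, n per group = 2 × SD² × (z for alpha + z for power)² / [ln(ratio/0.5)]². With one-sided alpha 0.025 and a coefficient of variation of 0.75, SD = √ln(1 + 0.75²) = 0.668. The noncentral-t version of this calculation gives 1034, 284, 138 and 84 for ratios 0.55, 0.60, 0.65 and 0.70, which are exactly the four rows of the GMT-ratio table in 3.8.2. The normal approximation gives 1033, 283, 137 and 83. One-sided alpha 0.05 fits about as well only with a log SD near 0.74. The table is therefore a non-inferiority calculation against 0.5.

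**Standard error at 138 per group.** SE = 0.668 × √(2/138) = 0.0804. The 95% limits are the observed ratio divided and multiplied by exp(1.96 × 0.0804) = 1.171.

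**The two rules at a true ratio of 0.65.**

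- Confidence-interval rule: ln(0.65/0.5)/0.0804 = 3.26, and Φ(3.26 − 1.96) = 0.90.
- Two-sided 5% test of equality: |ln 0.65|/0.0804 = 5.36, and Φ(5.36 − 1.96) is above 0.999.

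**At a true ratio of 0.80.**

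- Confidence-interval rule: ln(0.80/0.5)/0.0804 = 5.84, so power is close to 100%.
- Test of equality: |ln 0.80|/0.0804 = 2.77, and Φ(2.77 − 1.96) = 0.79. With log SD 0.745 it is about 0.70.

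**Where the two rules part.** An observed ratio of 0.65 has a 95% interval of 0.65/1.171 to 0.65 × 1.171, about 0.555 to 0.761. That excludes both 0.5 and 1. In general the interval excludes 0.5 when the observed ratio exceeds 0.5 × 1.171 = 0.585, and it excludes 1 from below when the ratio is under 1/1.171 = 0.854. Between 0.585 and 0.854 both hold.

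**Direction of the error.** A two-dose disadvantage is non-significant only if the observed ratio is above 0.854. Any such ratio also exceeds 0.585 and so meets the 0.5 limit. At this sample size, misreading the t-test can withhold a non-inferiority conclusion but cannot create a false one.

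**Sample size under the confidence-interval rule.** 138 per group gives 90% power, as planned. Expected retention is 250 × 0.80 × 0.95⁵ = 155 to 250 × 0.90 × 0.95⁵ = 174 per group. If the table was instead built at one-sided 5% with log SD 0.745, a two-sided 95% interval gives Φ(0.2624/(0.745 × √(2/n)) − 1.96): about 83% at n = 138, 87% at 155 and 91% at 174.

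**Month-60 titre as a covariate.** The required n falls by the factor 1 − ρ², where ρ is the correlation between log titres at months 60 and 120. The documents give no ρ. As an assumed range, ρ = 0.3, 0.5 and 0.7 give about 126, 104 and 71 per group, or power at 138 of about 93%, 96% and 99.5%.

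**The case against.** The best defence is that the protocol does have a criterion. Section 3.8.2 sets it, section 3.9 never says that the t-test's null hypothesis is equality, and a t-based interval on log titres compared with 0.5 is a valid non-inferiority analysis. This stands in part. A reader might infer that the named methods can never show non-inferiority; for GMTs that goes too far. What is missing is the link from 3.9 to the 0.5 limit. For seropositivity the defence fails, because there is no margin to link to.

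It can also be said that being non-inferior to 0.5 and different from 1 are compatible findings, and that objectives 2.2.a and 2.2.c only ask for a comparison. That is true, but section 3.9 itself states non-inferiority as the purpose and does not say which result decides.

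Three stronger readings are not supported by the document:

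- That the month-60 titre is ignored. It is analysed: "Among seropositive samples, GMTs will be calculated for each of the 3 time points planned in the protocol". It is only not used as a covariate, which in a randomised comparison costs precision and not validity. Section 3.3 places that blood sample at the randomisation and dosing visit but does not say whether it precedes the injection.
- That the ANOVA treats the three months as independent. The wording also fits a separate ANOVA at each month or a repeated-measures ANOVA. With one ANOVA per month, Duncan's test on two groups adds nothing to the t-test. Applied to all group-by-month means without allowance for repeated measurements, it would ignore within-girl correlation, and it does not control familywise error. Neither use tests the 0.5 limit.
- That baseline adjustment would save a known number of girls. Any saving depends on an assumed correlation, taken as equal in both groups although one receives a third dose at month 60.

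**Conclusion.** The point holds in a limited form. Section 3.9 states a non-inferiority purpose and names procedures that, taken as tests of equality, do not address it. The criterion that sized the subset is not carried into the analysis, and seropositivity non-inferiority cannot be tested as the protocol stands.

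For GMTs the consequence is one-sided: a justified conclusion may be withheld over a wide band of plausible results. For seropositivity, an uninformative non-significant result may be over-read.

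The figures rest on a log SD of about 0.67, back-solved from a table that it reproduces in full. The alternative of about 0.745 leaves the conclusion unchanged. This is a secondary objective with a cheap remedy, so the text should be amended; the primary analysis is not affected.

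**What to change.** In section 3.9:

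- State that month-120 non-inferiority is concluded if the lower limit of the two-sided 95% confidence interval of GMT2/GMT3, computed from log titres, exceeds 0.5. Preferably adjust for the log month-60 titre, and state whether that sample is drawn before the injection. The adjustment is a precision gain of unknown size and corrects no bias.
- Report seropositivity as a difference between groups with its 95% confidence interval. Either give it a margin, set before the month-120 results are seen, or label it descriptive.
- Drop Duncan's test or label it descriptive, and say that the t-test of equality does not decide non-inferiority.
- Require any analysis across months to account for repeated measurements on the same girl. A full longitudinal model is one option but is not needed for the month-120 conclusion.

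In section 3.8.2, state the sidedness of alpha and the SD used, so that the 138 per group is visibly tied to the two-sided 95% interval.

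The cost is protocol wording and slightly more analysis work. No new data are needed. N does not change if the table was built at one-sided 0.025, the setting that reproduces all four rows.

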## 4.2 Coordination

The coordination responsibilities will be divided between the CRCHU of Quebec and the CRCHUM. The study's principal research coordinators (nurses) will be based at the CRCHU of Quebec, where they are already working on longitudinal cohort studies. Vaginal samples will be sent to the CRCHUM (to [name] facilities) for analysis in [name] laboratory. Blood samples will be sent to the LSPQ or the CDC for analysis. Databases will be developed by the Applied Research Unit (URCA) of the CHU Sainte-Justine Research Center and deployed at both the CRCHUM and the CRCHU of Quebec. Nominal data from the Quebec City site will be stored on a secure server.

In addition to the study's principal coordinator, each center will have a coordinator responsible for the procedures specific to their site. The contact details of the participants will be kept at the research center where the initial visit was conducted. The self-sampling kits sent to participants will include a pre-paid return envelope addressed to the research center at the CRCHUM ([name] facilities) and financial compensation (\$5.00 up to age 17 and \$10.00 starting at age 18, per sample). These shipments will originate from the coordinating center in Quebec City. Periodically, the samples will be transferred to [name] virology laboratory at the CRCHUM for analysis. After recruitment is complete, participant follow-up will be managed by the coordinating center in Quebec. This includes follow-up reminders via email or phone and other email communications.

## 4.3 Calendar

Protocol Submission: REB CRCHUM and CRCHU of Quebec, January 2013

Final Protocol Approval: February-March 2013

Start of CAI and RAMQ Procedures: December 2012

Expected Decisions from CER, CAI, and RAMQ: April 2013

RAMQ Data Acquisition: August 2013

### Vaccinated girls who started vaccination in 2008

Mailings: September 2013–April 2014  
Call returns: September 2013–June 2014

Recruitment/Randomization Visits: September 2013–June 2014

End of Follow-Up: 2021

### Vaccinated girls who started vaccination in 2009

Mailings: May 2014–April 2015

Call returns: May 2014–March 2015

Recruitment/Randomization Visits: May 2014–June 2015

End of Follow-Up: 2021

### Vaccinated girls who started vaccination in 2010

Mailings: May 2015–April 2016

Call returns: May 2015–March 2016

Recruitment/Randomization Visits: May 2015–June 2016

End of Follow-Up: 2021

### Vaccinated girls who started vaccination in 2011

Mailings: May 2016–December 2016

Call returns: May 2016–December 2016

Recruitment/Randomization Visits: May 2016–December 2016

End of Follow-Up: 2021

An interim analysis is planned 5 years after the recruitment of the first participants (2018).

Study closure, analysis, presentations, report, and publications: 2022.

## **5. Ethics considerations**

There are specific ethical challenges related to the enrolment of minors. However, the enrolment of minor is essential to meet our primary research question. Girls aged 18 years or more are (1) not targeted by the vaccination program(20); (2) they do not have the same response to the vaccine as younger girls(25,26) and (3) on average, they have a sexual experience that is very different from younger teenagers(92). Our team has vast experience in the enrolment and retention of this type of participant(91,93–95). We will first contact the girls' parents and they will decide to present the project to their child or not. Then a member of the team (nurse) will make sure to obtain both the parents' and the girls' consent. Randomization is explained by the state of «clinical equilibrium» on the primary research question. The risks associated with the intervention are well known by the girls and their parents given that they have already received two doses of Gardasil®. These are mainly local side effects as redness and pain at the injection site(20).

Given the immunogenicity and efficacy data which are available, the primary research hypothesis is that a schedule with 2 doses administered at a 6 month interval is non-inferior to a 3-dose schedule (0, 6, 60 months). If on the contrary, the non-inferiority of the 2-dose schedule could not be demonstrated, the girls in the 2-dose group will be offered a 3rd dose free of charge at the end of the study or at any other time fixed by the research team and the monitoring committee.

### **5.1 Confidentiality**

All identifying data will be stored on a secure and dedicated server, protected by a password. These files will be kept separate from all results. During recruitment, participants will be assigned a study code, which will subsequently be used to identify all their samples and questionnaires. The key linking the study code to the participants will be kept separately on a dedicated server at the coordinating center. Only the study's coordinators will have access to it.

### **5.2 External committee**

An external committee for study overview and data monitoring will be set up. It will consist of methodologists and content experts. The committee will meet once a year.

## 6. Expected impact

The information collected in this study will first enable us to make an informed decision (relying on efficacy data) on the usefulness of a 3rd dose of HPV vaccine.

This study will also help to have a better knowledge of the role of antibody titers in the acquisition of HPV persistent infections and might contribute to the establishment of a protective threshold. HPV vaccination has been highly effective(25). Therefore, occurrence of infections among vaccinees was not high enough to measure an antibody level that could be considered as protective against HPV-related clinical outcomes (condylomas, precancer or cancer). The analysis of immunogenicity and efficacy of HPV vaccination within the same study is essential. This approach will enable the measurement of the immune response (antibody testing) following vaccination and following natural infection. The antibody level maintained when no natural infection was detected will equally be informative. These various elements might help to determine the level of antibody needed to prevent a persistent infection.

Finally, we will better describe sexual behaviors, some lifestyles, cervical cancer screening and link this information with the occurrence of persistent infections. There is no doubt that this better portrait will help improve strategies for the prevention of cervical cancer.

## 7. Extension : phase 2

Depending on available funding, the research team will plan a 3-year extension (phase 2) of this research project resulting in a total of 8 years of follow-up. The same objectives will be maintained until the participants are aged 22-23 years and the following objective will be added:

To explore if a schedule with 2 doses administered at 0, 6 months is non-inferior to a schedule with 3 doses administered at 0, 6, 60 months for the prevention of precancerous and cancerous lesions identified during cervical cancer screening and this until 13 year following the beginning of vaccination.

